### Recruitment

This study will enroll patients with AGC who received NACT before laparoscopic or robotic radical gastrectomy from 22 centers, as listed in Table 1. The launching conference was held to ensure that the details of the GISSG 2023–01 trial will be known by every investigator. There are three approaches to recruit patients: patients from outpatient departments, patients from oncology departments and patients referred from local hospitals who have finished NACT and plan to receive surgical treatment. All investigators from 22 centers were informed that the clinical trial had begun and that the participants should know all details about the trial to obtain an adequate number of participants. The enrollment of the first patient was started in April 2023, and it is anticipated that the deadline for the recruitment of the patients will be in April 2024. Ultimately, 318 patients who meet the inclusion criteria will be included in this trial and randomized into a probiotic group and a control group in a 1:1 ratio. A conference for all investigators will be held bimonthly for communication about difficulties and experiences during recruitment and for deciding whether to improve the study protocol.

### Assignment of interventions

A central dynamic, stratified strategy was adopted for the aim of randomization. The sequence of randomization was generated by a certain statistician who was independent of this trial using the method of Pocock-Simon minimization by SAS 9.3 (SAS Institute Inc., Cary, NC, USA) and stratified by age (< 65 years old or ≥ 65), tumor location (upper, middle or lower) and preoperative chemotherapy cycles (2 or ≥ 2 cycle). The stratification information provided by the investigators was submitted to the statistician who was responsible for executing randomization. Consequently, the allocation information will then be sent back to each participating site, and investigators will assign given interventions. The statistician is the only one who will know the allocation sequence to ensure that the sequence is concealed until the interventions are assigned.

Due to the open-label design of this study, no one will be blinded after assignment to interventions. After receiving the allocation information, investigators from every participating center will assign the given interventions to participants.

## Data collection, management, and analysis

### Data collection methods and management

All data will be entered into an electronic data capture (EDC) system and recorded on a paper case report form (CRF). Subaccounts will be assigned to participating by the sponsor-investigator, and every modification will be recorded in the background of the EDC to ensure facticity. The CRF should be sent back to sponsor-investigator for cross check. An independent statistician is responsible for collecting the data and is unaware of the participants'group assignments.

### Statistical methods

The Shapiro‒Wilk test will be used to verify the normality of the quantitative variables. To describe the quantitative variables, the mean and SD will be used, and the median and interquartile range will be used for those variables that do not follow a normal distribution. For qualitative variable descriptions, frequencies and percentages will be used. A contrast test of proportions will be based on the *χ*^*2*^ test or Fisher’s exact test. Quantitative variables will be analyzed by Student’s *t* test or two-way repeated-measures analysis. The Mann‒Whitney *U* test will be used for variables that do not follow a normal distribution. The results will be analyzed using SPSS version 24 (IBM, Armonk, NY, USA), and *P* < 0.05 will be considered statistically significant. The mean of each variable will be used to replace missing data.

A modified intention-to-treat analysis (mITT) and per-protocol (PP) analysis will be used to compare outcomes, but the conclusion will be drawn from mITT analysis.

The mITT population is defined as subjects who are screened by investigators according to the inclusion and exclusion criteria, randomized into certain groups and receive at least one intervention. The PP population is defined as those who complete the given intervention, adhere to the study protocol and complete the data collection. Subgroup analysis will be executed based on the operation platform (laparoscope or DaVinci surgical robot), preoperative chemotherapy regimens (SOX, DOS, XELOX, FLOT or others), GI restruction and resection range (proximal, distal or total gastrectomy).

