#### Eligibility criteria

Patients with AGC who have completed NACT will be screened for eligibility.

The inclusion criteria are as follows: 18–80 years old; both male and female; clinical stage of T3/4 N + evaluated by CT/MR/EUS at new diagnosis (before any anticancer treatment), completion of 2–4 cycles preoperative chemotherapy based on 5-FU (such as SOX, XELOX, FLOT, etc.) at 3–6 weeks before surgery; ASA grade of I-III; radical minimally invasive gastrectomy via a laparoscope or a DaVinci surgical system judged as possible; histologically confirmed gastric adenocarcinoma; ECOG score of 0 ~ 1; and provision of written informed consent before entering the study screening process.

The exclusion criteria are as follows: need for emergency surgery due to perforation and/or obstruction; receipt of antibiotics and/or glucocorticoids within 14 days before surgery; presence of bacterial infection and/or autoimmune disease and/or IBD; intolerance or allergy to probiotics; major upper abdominal surgery history (for example laparoscopic cholecystectomy); use of probiotics within 7 days before the intervention; current participation in other clinical trials; severe mental illness; inability to participate in this trial due to severe disease of other organs evaluated by researchers, such as severe cardiac insufficiency (LVEF < 30%, NYHA > II, severe arrhythmia, congestive heart failure, myocardial infarction within 6 months), liver dysfunction (Child‒Pugh C), renal dysfunction (need for hemodialysis); need for simultaneous surgery; lactation or pregnancy; refusal to participate in this trial.

Patients from the 22 hospitals will be evaluated, and those who meet the eligibility criteria will be invited to participate in the study. Patients will decide whether they are willing to participate in this study, and for those participants, written informed consent will be required.

The surgeons who perform the minimally invasive radical gastrectomy for the participants will also be evaluated. They should have performed more than 100 DaVinci robotic or laparoscopic radical gastrectomies and send an unedited operation radio to the sponsor investigators to verify their capacity.

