### Outcomes

The primary outcome is the incidence of postoperative infectious complications, which are defined as bacterial infections occurring within 30 d after surgery. The definition of infectious complications is based on fever (≥ 38 °C), elevation of C-reactive protein (CRP), specific clinical symptoms of infection and positive bacterial culture. The diagnostic criteria for postoperative infections in this study are as follows. Pneumonia [25]: fever, cough, dyspnea, reduced arterial oxygen, typical pulmonary infiltrate on chest X-ray, positive culture from sputum or bronchoalveolar lavage. Urinary tract infection: obvious symptoms including frequent micturition, urgency to urinate, urodynia, leukocyturia, and a positive urine culture with > 10^5^ CFU/ml. Incision infection: redness or swelling of the incision, subcutaneous gas accumulation and purulent secretion and positive culture of incisional secretion [26]. Intraabdominal infection [27]: abdominal symptoms and positive signs such as abdominal pain, tenderness, rebound tenderness, radiographic evidence including intra-abdominal abscess, positive bacterial cultures from intra-abdominal smears or abdominal drainage fluid. Catheter-related blood stream infection: refer to the guidelines [28]. Systemic inflammatory response syndrome (SIRS): two or more of the following: a, temperature > 38 °C or < 36 °C; b, heart rate > 90/min; c, respiratory rate > 20/min or PaCO2 < 32 mm Hg (4.3 kPa); d, white blood cell count > 12 000/mm^3^ or < 4000/mm^3^ or > 10% immature bands [29]. The diagnosis of sepsis should follow the *Sepsis- 3 Consensus* [30].

Secondary outcomes for all participants include blood test results, such as the leukocyte count (WBC), percent of neutrophils (NEUT%), CRP and procalcitonin on PODs 1, 3, and 5; postoperative body temperature; length of postoperative hospital stay (LOS); total cost of hospitalization; 30-d readmission rate; 30-d mortality rate; duration of therapeutic antibiotic use; time to first flatus, first bowel movement and solid food tolerance; time to initiating adjuvant chemotherapy; EORTC QLQ-C30 score [31] on POD 30; PGSAS- 45 score [32] on PODs 3, 5 and 30; and visual analogue scale for pain evaluation on PODs 1, 3 and 5.

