### Sample size

The sample size calculation was based on postoperative infection. Based on the results of our previous single-center RCT, the rates of postoperative infectious complications were 39.4% in the control group and 15.2% in the probiotic group. Given a significance one-sided level of *α* = 0.025 and test efficiency of 1 − *β* = 80%, a loss adjustment of 10% and a superiority threshold of 10%, the total sample requires at least 318 patients (159 in the test group and 159 in the control group on a 1:1 allocation ratio). The Test for Two Proportions (Non-Zero Null Hypothesis[Differences]) was used for sample size calculation (Hintze, J. (2011). PASS 11. NCSS, LLC. Kaysville, Utah, USA. www.ncss.com/).

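### The primary comparison ignores the three minimisation factors, so it is valid but mildly conservative; the cycles factor is also printed with overlapping levels

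*Protocol article*

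**What the plan says.** All references are to the protocol article.

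- **Assignment of interventions.** The allocation sequence was generated "using the method of Pocock-Simon minimization by SAS 9.3". The factors are age (below 65, or 65 and over), "tumor location (upper, middle or lower") and "preoperative chemotherapy cycles (2 or ≥ 2 cycle"). Investigators submit the stratification information to one independent statistician, who runs the randomisation.
- **Eligibility criteria.** Patients enter after "completion of 2–4 cycles preoperative chemotherapy based on 5-FU".
- **Outcomes.** "The primary outcome is the incidence of postoperative infectious complications" within 30 days of surgery, so the primary variable is binary.
- **Statistical methods.** "A contrast test of proportions will be based on the" chi-square test or Fisher's exact test. Quantitative outcomes get the t test, repeated-measures analysis or the Mann-Whitney test. No regression or stratified test is named, and the subgroup list contains none of the three minimisation factors.
- **Sample size.** The assumed rates are "39.4% in the control group and 15.2% in the probiotic group", tested at one-sided 0.025 with 80% power against a 10-point superiority threshold. With 10% loss this gives 318 patients.

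**The concern.** Minimisation makes the arms more alike on the chosen factors than simple randomisation would. If those factors predict infection, the difference in infection rates between arms varies less from trial to trial. An unadjusted chi-square computes its standard error as if the balancing had not been done. The standard error is then too large, the actual type I error falls below the nominal level, and precision that the design has bought goes unused.

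The second matter is textual. Every eligible patient has 2 to 4 cycles, so every one meets the level written as at least 2, and a patient with exactly 2 cycles fits both levels. As printed, the factor neither separates patients nor can serve as a covariate.

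**Working it through.** **1. The plan's own figure.** Inputs from Sample size: control rate 0.394, probiotic rate 0.152, margin 0.10, one-sided alpha 0.025, power 0.80, loss 10%.

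- Variance term: 0.394 × 0.606 + 0.152 × 0.848 = 0.3677.
- Distance from the margin: 0.242 − 0.10 = 0.142.
- n per arm = 0.3677 × (1.960 + 0.842)² / 0.142² = 143.1.
- Loss: 143 / 0.9 = 158.9, so 159 per arm and 318 in total. Rounding 143.1 up to 144 first gives 160 per arm, 320 in total.

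The stated 318 is therefore reproduced. Nothing below changes it.

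**2. Type I error of the unadjusted test.** The documents do not say how strongly the factors predict infection, so the share of outcome variance explained (R²) is an assumption, shown as a range. If minimisation balances the factors closely, the true variance of the arm difference is about (1 − R²) times the variance that the chi-square uses. The actual two-sided error is then 2 × [1 − Φ(1.96 / √(1 − R²))].

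| Assumed R² | 1.96 / √(1 − R²) | Actual type I error |
|---|---|---|
| 3% | 1.990 | 4.66% |
| 5% | 2.011 | 4.43% |
| 10% | 2.066 | 3.88% |

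**3. Power of the margin test, 143 evaluable per arm.** Unadjusted standard error = √(0.3677 / 143) = 0.0507. Power = Φ(0.142 / 0.0507 − 1.960) = 80.0%. With adjustment the standard error is multiplied by √(1 − R²).

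| Assumed R² | Standard error | Power |
|---|---|---|
| none (unadjusted) | 0.0507 | 80.0% |
| 3% | 0.0499 | 81.2% |
| 5% | 0.0494 | 81.9% |
| 10% | 0.0481 | 83.9% |

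**4. Power of the chi-square as written.** It tests a difference of zero. At 39.4% versus 15.2% with 143 per arm its power is 99.7%, so at the design rates there is almost nothing to gain.

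**5. Simulation check.** Minimisation on three factors was simulated (two, three and two equally likely levels; the favoured arm chosen with probability 0.8) with 2 × 143 = 286 evaluable patients, a control rate of 39.4% and 6,000 replicates per scenario. The unadjusted chi-square was compared with logistic regression on the three factors, both two-sided at 0.05. Prognostic strength is an assumed odds ratio per factor level. Power is for an illustrative smaller effect, 39.4% versus 25%.

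| Odds ratio per level | Type I error, unadjusted | Type I error, adjusted | Power, unadjusted | Power, adjusted |
|---|---|---|---|---|
| 1.0 | 4.7% | 4.9% | 75.1% | 75.3% |
| 1.5 | 4.3% | 5.1% | 75.8% | 77.1% |
| 2.0 | 3.3% | 4.8% | 76.5% | 79.8% |
| 3.0 | 2.2% | 4.7% | 77.0% | 83.5% |

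The Monte Carlo standard error near 5% is √(0.05 × 0.95 / 6000) = 0.3 points, so the first row shows no real difference. The direction agrees with step 2. The gain runs from about 0 to 6.5 points of power, and its upper end needs every factor level to carry an odds ratio of 3.

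**6. The cycles factor.** Eligible values are 2, 3 and 4. The first printed level contains {2} and the second contains {2, 3, 4}. The value 2 lies in both. The only nearby reading that separates patients is 2 versus more than 2.

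**The case against.** The strongest reply is that little is at stake. The chi-square is a valid test here and every error rate above is at or below 5%. With weak factors (R² of 3% to 5%, or odds ratios up to 1.5 per level) adjustment brings one or two points of power. All of this stands.

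Three stronger readings are tempting, and the documents do not support them.

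- **That the trial's error rate is compromised.** The departure from 5% is in the conservative direction. False positives are not inflated.
- **That the chi-square loses power from 84% to 80%.** Those figures belong to the 10-point margin test in Sample size. The chi-square in Statistical methods, as written, tests zero difference and has about 99.7% power at the design rates.
- **That sites coded identical patients differently, leaving the arms unbalanced on chemotherapy.** Randomisation was run centrally by one statistician. Sites may simply have reported the number of cycles, and nothing shows that the overlapping levels were used.

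It can also be said that covariate adjustment is often settled in a statistical analysis plan, which is not shown. The article does not rule adjustment out. But it does not defer the choice either: it names the test for proportions, and that test is unadjusted.

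Lastly, Trial status reports that recruitment is complete and that the trial ended during peer review, so a new primary analysis would come late. This limits the remedy, and the fix allows for it.

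**Conclusion.** The point holds as one of efficiency, not validity. The only test stated for the primary outcome leaves out the factors used in allocation. The cost is a type I error of about 3.9% to 4.7% instead of 5%, and about 1 to 4 points of power on the margin test, for an assumed R² of 3% to 10%. The size rests wholly on that assumption and would be close to zero if the factors do not predict infection. It matters most if the claim is made against the 10-point margin, or if the true effect is smaller than the single-centre estimate.

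The overlap in the cycles levels needs no assumption: it is an error in the text as printed. It is probably a slip for 2 versus more than 2. It calls for clarification, and it is not evidence that allocation failed.

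**What to change.** 1. **If the data have not yet been analysed by arm:** specify a primary analysis adjusted for age group, tumour location and cycles, for example logistic regression reported as a standardised risk difference with a 95% confidence interval. Keep the chi-square or Fisher test as supportive. State whether the null is zero or the 10-point margin, since the sample size and the named test differ on this.
2. **If outcomes have already been seen by arm:** leave the published test as primary and report the adjusted analysis as a labelled sensitivity analysis. The monitoring section releases interim results to all investigators, so record what was seen, and when, before choosing between 1 and 2.
3. **Cycles factor:** state the levels actually used in the minimisation, check how patients with exactly 2 cycles were entered, and use the recorded number (2 versus 3 to 4) as the covariate. Completed allocations cannot be altered.

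No new patients are needed. The factors were submitted at randomisation, so the cost is a dated change to the analysis text, a check of the allocation records and one additional model.

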**Fig. 1 Fig1:**
[figure not shown]
The enrollment, intervention and assessment items in the flowchart. The symbol × represents that the program needs to be collected. − 1, the end of the last cycle of preoperative chemotherapy; 0, from the end of the last cycle of preoperative chemotherapy to admission for surgery; D1, postoperative day 1; D2, postoperative day 2; D3, postoperative day 3; D4, postoperative day 4; D5, postoperative day 5; D6, postoperative day 6; D7, postoperative day 7; D30, postoperative day 30; Dp, prolonged postoperative hospital stay; * the majority of participants can be discharged before D7 under the ERAS perioperative management protocol, but if any situation prolongs the hospital stay, the marked items should be recorded and described on the CRF

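### Filling every missing value with the variable's mean cannot work for the binary primary outcome, and for continuous outcomes it either understates the standard error or shrinks the difference

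*Protocol article*

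**What the plan says.** The Statistical methods section of the protocol article states the rule in one sentence: "The mean of each variable will be used to replace missing data". It names no class of variable to which the rule does not apply, does not say over which patients the mean is taken, and gives no alternative or sensitivity analysis. The same section has mITT and per-protocol analyses and draws the conclusion from mITT.

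The rule meets three kinds of outcome:

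- **Binary primary outcome.** Under Outcomes: "The primary outcome is the incidence of postoperative infectious complications, which are defined as bacterial infections occurring within 30 d after surgery". The sentence on proportions ("A contrast test of proportions will be based on the") goes on to name the chi-square and Fisher's exact tests.
- **Repeated continuous measures.** Examples are "percent of neutrophils (NEUT%), CRP and procalcitonin on PODs 1, 3, and 5", together with pain and PGSAS-45 scores. Quantitative variables are to be analysed by the t "test or two-way repeated-measures analysis", or by Mann-Whitney if not normal.
- **Times to an event.** These are "time to first flatus, first bowel movement and solid food tolerance; time to initiating adjuvant chemotherapy".

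**The concern.** A mean is a possible value for a laboratory marker but not for an infection status. Applied as written to the primary outcome, the rule produces a number that the named tests cannot use, so someone must improvise, and the obvious improvisation (rounding) decides the status of every missing patient in one direction.

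Missing primary outcomes are foreseeable. Treatment starts after the last chemotherapy cycle, which Eligibility criteria places 3–6 weeks before surgery, while mITT asks only for randomisation and at least one intervention. A patient who never reaches surgery can therefore be in mITT without a postoperative outcome.

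For continuous outcomes, single mean filling treats invented values as observed. What goes wrong depends on which mean is used, and the text leaves that open. For the times to an event, a patient who had no event would receive an average time if the non-event is recorded as missing.

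**Working it through.** **Inputs.** From Sample size: infection 39.4% (control) and 15.2% (probiotic), one-sided α 0.025, power 80%, threshold 10 points, loss 10%, 159 per arm. The article gives no missing rate other than the loss allowance, so the missing share m is an assumption. I use 5% and 10%.

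**1. The plan's own figure.** With unpooled variance:

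- Variance sum = 0.394×0.606 + 0.152×0.848 = 0.3677.
- n = 0.3677 × (1.960 + 0.842)² / (0.242 − 0.10)² = 143.1 per arm.
- 143.1 / 0.9 = 159.0 per arm, or 318 in total. The stated size is reproduced. (Rounding up to 144 before adding the loss gives 160 per arm.)

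**2. Primary outcome: the filled value.** The overall mean at equal arms is (0.394 + 0.152)/2 = 0.273. The arm means are 0.394 and 0.152. All are fractions, and all round to 0, that is, not infected.

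**3. Primary outcome: effect of rounding.** With the same share m missing at random in each arm, each rate is multiplied by (1 − m). Power against the threshold is Φ[(difference − 0.10)/SE − 1.96], where SE² = [p₁(1 − p₁) + p₂(1 − p₂)]/n.

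| m | Rates after filling | Difference | Power, filled (n = 159) | Power, observed cases only (n = 159(1 − m)) |
|---|---|---|---|---|
| 5% | 37.4% / 14.4% | 23.0 points | 78% | 82% |
| 10% | 35.5% / 13.7% | 21.8 points | 71% | 80% |

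At 10%, SE = √(0.3470/159) = 0.0467 and (0.2178 − 0.10)/0.0467 − 1.96 = 0.56, so power is 71%.

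If the shares differ, the expected difference is 39.4(1 − m_control) − 15.2(1 − m_probiotic). Loss in the control arm lowers it and loss in the probiotic arm raises it, so the bias can go either way.

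**4. Continuous outcome, arm mean.** The within-arm sum of squares is unchanged but is divided by about n instead of n(1 − m), and the SE formula again uses n instead of n(1 − m). The naive SE is therefore (1 − m) times the correct one. Two-sided type I error is 2[1 − Φ(1.96(1 − m))]:

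- m = 5%: 2[1 − Φ(1.862)] = 6.3%.
- m = 10%: 2[1 − Φ(1.764)] = 7.8%.

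Simulation (20,000 runs, 159 per arm, normal outcome, missing completely at random) gave 6.2% and 7.8%.

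**5. Continuous outcome, overall mean.** Each filled arm mean is (1 − m) × arm mean + m × overall mean, so the difference is multiplied by (1 − m). In the simulation, 0.320 SD became 0.304 at 5% missing and 0.321 SD became 0.289 at 10%. Under no difference, type I error was 5.0% and 4.8%, because the estimate and its SE shrink together.

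**The case against.** Several points on the other side are fair.

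- **The sentence may be meant for quantitative variables only.** The section otherwise uses the mean for those and percentages for qualitative variables. That is possible, but the sentence says each variable and sets no limit. The ambiguity itself needs correcting.
- **No rounding is specified.** True. The 21.8 points and 71% describe one way of making the rule workable. Without rounding, the named tests cannot be run on the filled data at all.
- **The power loss concerns the 10-point threshold only.** Against a difference of zero, the filled data give 0.2178/0.0467 − 1.96 = 2.70, so power stays above 99%. With equal loss, rounding also biases towards no difference. This limits the harm but does not make the rule usable.
- **The per-protocol set requires completed data collection** and so largely avoids filled values. But it does not decide the conclusion.

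A reader might also infer more than the article supports:

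- **That false positives rise in general.** This needs the arm-mean reading, which is not stated. Data collection and management says the statistician collecting the data is unaware of group, which fits an overall mean at least as well.
- **That inpatient markers will be missing mainly in patients who went home early.** The Fig. 1 legend says "the majority of participants can be discharged before D7 under the ERAS perioperative management protocol", but the last inpatient laboratory and pain assessments are on day 5, and nothing says that patients leave before then.
- **That 20% or more of values will be missing, or that loss will fall on one arm only.** The article gives only a 10% loss allowance for the sample size, which is not a missing rate per variable.
- **That patients who never start adjuvant chemotherapy will certainly receive an average start time.** This follows only if a non-event is coded as missing, which the article does not say.

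**Conclusion.** The concern holds in limited form. The article fixes a rule that, as worded, cannot be applied to the binary primary outcome at any missing share, and that rule feeds the deciding analysis. This is a method stated badly, not a detail left to an analysis plan.

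The size rests on assumptions. With 10% missing at random in both arms and rounding, the rule costs 2.4 points of the planned difference and about 9 points of power against the threshold. For continuous outcomes the harm is false precision under an arm mean, or attenuation under an overall mean, and the text does not settle which. Below 5% missing the effects are small. Which test suits the times to an event is a separate question. The point here is only that no time should be invented for an event that did not occur.

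**What to change.** Delete the mean-replacement sentence and state a rule for each type of outcome:

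- **30-day infection:** multiple imputation by arm, including the minimisation factors (age group, tumour location, chemotherapy cycles), with a best/worst-case or tipping-point sensitivity analysis.
- **Repeated laboratory, pain and PGSAS-45 values:** a likelihood-based mixed model on the observed data, without filling.
- **Times to flatus, bowel movement, solid food and adjuvant chemotherapy:** no average time for patients without the event. Treat them as censored or as non-events, and say which.

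The number missing should be reported by arm for each outcome. The cost is wording and some extra programming, with no new data. Trial status says the trial has ended, so the change should be dated and reported as a change from the published plan.

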### Interventions, surgery and perioperative management

Patients in the probiotic group will receive three probiotic capsules (BIFICO, live combined *Bifidobacterium*, *Lactobacillus* and *Enterococcus* capsules, Shanghai Sine Pharmaceutical Co. Ltd., [name], Shanghai, China) containing *Bifidobacterium longum, Lactobacillus acidophilus,* and *Enterococcus faecalis* twice per day. Each capsule will contain > 1 * 10^7^ colony-forming units (CFUs) of live bacteria. Patients in the control group will be managed with a blank control. The intervention duration will begin from the end of the last cycle of NACT to postoperative day (POD) 7 or the discharge day. Adherence to the intervention protocols will be checked by telephone before admission to the surgical departments and making the rounds of the wards after admission. If any adverse event associated with the intervention occurs, the intervention will be stopped after evaluation by the investigators.

All enrolled patients will adhere to a perioperative enhanced recovery after surgery (ERAS) protocol [23]. The ERAS program involves preoperative prehabilitation [24] (including physical and respiratory training, nutritional support and psychosocial treatment), no preoperative mechanical bowel preparation, fasting 6 h before surgery and oral glucose solution ingestion allowed until 2 h before surgery, intraoperative target-oriented liquid management, local anesthesia in the deep incision, general anesthesia combined with epidural anesthesia, early removal of the urinary catheter and abdominal drainage tube, early bedside activity, multimodal postoperative analgesia, and postoperative early food ingestion under the guidance of surgeons (from liquid to semi-liquid then solid food according to the tolerance of patients).

Laparoscopic or DaVinci robotic radical gastrectomy will be performed by surgeons from the 22 hospitals whose capacity evaluation is described above. Surgical procedures will be guided by *Japanese Gastric Cancer Treatment Guidelines 2021 (6 th edition)* [2]. The type of digestive tract reconstruction will depend on the habits, intraoperative status and past experience of the surgeons, and the choice of laparoscopy- or DaVinci-assisted surgery will depend on the patients’ choice.

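### The primary (mITT) set drops probiotic patients who take no capsule, while a blank-control patient cannot fail the same condition, so the post-randomisation exclusion is one-sided

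*Protocol article*

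**What the plan says.** Statistical methods defines the mITT population as patients screened against the eligibility criteria, "randomized into certain groups and receive at least one intervention". It names a per-protocol set as well, "but the conclusion will be drawn from mITT analysis". No analysis of all randomised patients is named.

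The section on interventions, surgery and perioperative management describes the two arms. For the active arm: "Patients in the probiotic group will receive three probiotic capsules". For the other: "Patients in the control group will be managed with a blank control". No placebo is described. On timing: "The intervention duration will begin from the end of the last cycle of NACT to postoperative day (POD) 7 or the discharge day". Eligibility criteria places completion of chemotherapy "at 3–6 weeks before surgery".

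Assignment of interventions states that "no one will be blinded after assignment to interventions". Under Outcomes, the primary endpoint is infectious complications, "which are defined as bacterial infections occurring within 30 d after surgery".

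**The concern.** A condition of at least one dose is usually harmless where both arms have something to take and nobody knows the allocation, because failing to start cannot then depend on the arm. Neither holds here. Only the probiotic arm has a product that can be left untaken, and patient and investigator both know the allocation when capsules should begin, weeks before surgery.

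Patients who never start may differ from those who do. If they are removed from one arm while their counterparts stay in the other, the groups compared are no longer those formed by randomisation. This affects the analysis that carries the conclusion, and the per-protocol set cannot act as a check because it is more selective still.

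**Working it through.** **1. The plan's own figure.** Inputs from Sample size: 39.4% control, 15.2% probiotic, one-sided α 0.025, power 80%, superiority threshold 10 points, 10% loss. With unpooled variance:

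n = [0.394×0.606 + 0.152×0.848] × (1.960+0.842)² / (0.242−0.10)² = 0.3677 × 7.849 / 0.02016 ≈ 143.1 per arm.

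Allowing for loss, 143/0.9 = 158.9, i.e. 159 per arm and 318 in total. Rounding up to 144 first gives 160 per arm. The stated 318 is reproduced within rounding, so the sample size is not at fault.

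**2. Who can fail the condition.**

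| | Probiotic arm | Control arm |
|---|---|---|
| Study product | capsules | none |
| Can a patient fail to receive at least one intervention? | yes, by taking no capsule | no |
| Allocation known when capsules are due to start? | yes | yes |

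If *intervention* meant surgery, both arms could fail. However, Trial design and the interventions section use the word for something that runs from the end of chemotherapy to postoperative day 7 or discharge, and they describe surgery separately.

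**3. Bias from the one-sided exclusion.** Let p be the infection risk in each full arm when the probiotic has no effect, e the share of the probiotic arm that never starts, and r the infection risk of those patients.

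- Rate among starters = (p − e·r)/(1 − e)
- Spurious benefit = p − (p − e·r)/(1 − e) = e(r − p)/(1 − e)

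The bias is zero when r = p, favours the probiotic when r > p, and goes against it when r < p.

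Take p = 0.394 from Sample size. The documents give neither e nor r, so e = 2%, 5%, 10% and r = 39.4%, 50%, 60% are assumptions. One-sided type I error against zero difference is 1 − Φ(1.960 − bias/SE), where SE² = p(1−p)/159 + p_s(1−p_s)/n_s, p_s is the starters' rate and n_s = 159(1−e), rounded.

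| e | r | Starters' rate | Spurious benefit (points) | n_s | Type I error |
|---|---|---|---|---|---|
| any of the three | 39.4% | 39.4% | 0 | – | 0.0250 |
| 2% | 50% | 39.2% | 0.2 | 156 | 0.0274 |
| 2% | 60% | 39.0% | 0.4 | 156 | 0.0298 |
| 5% | 50% | 38.8% | 0.6 | 151 | 0.0315 |
| 5% | 60% | 38.3% | 1.1 | 151 | 0.0389 |
| 10% | 50% | 38.2% | 1.2 | 143 | 0.0400 |
| 10% | 60% | 37.1% | 2.3 | 143 | 0.0604 |

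Example, last row: (0.394 − 0.10×0.60)/0.90 = 0.371; bias 0.0229; SE 0.0560; 1.960 − 0.409 = 1.551, which gives 0.060.

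**4. Price of keeping non-starters.** At the design rates, with non-starters at the control risk and 159 per arm analysed, the probiotic rate is (1−e)×0.152 + e×0.394. The difference becomes 23.7, 23.0 and 21.8 points for e = 2%, 5% and 10%. Power against the 10-point threshold is 81%, 76% and 67%, compared with 84% if everyone starts.

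**The case against.** Five points can be made on the other side.

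- **A reader might infer that, taken literally, no control patient qualifies and the control arm is empty.** The article does not support this. Assignment of interventions says that investigators assign the given interventions to participants after receiving the allocation, which covers both arms. Blank control is thus treated as an assigned intervention. The point is the asymmetry, not an empty arm.
- **Non-starters may be few.** One dose is enough to enter the set, and dosing begins in consented patients straight after chemotherapy. A patient who deteriorates or progresses after a first capsule stays in. At 2% non-starters the bias in the table is 0.2 to 0.4 points. This stands.
- **A reader might infer a bias of several points by assuming much higher infection risks, or a bias in the other direction by counting unoperated controls as event-free.** Nothing in the documents supports such risks, and the event-free rule is not stated. The only missing-data rule is replacement by the variable's mean. How unoperated patients count is a separate gap that any revised set must settle.
- **The 10-point threshold might absorb the bias.** If it were applied, the last row of the table would pass under no true effect only with probability Φ((2.29−10)/5.60 − 1.96) = Φ(−3.34), about 0.0004. But Statistical methods states a χ² or Fisher test at P < 0.05 and does not mention the threshold. Error at a true 10-point difference would in any case still be affected.
- **A set restricted to patients who undergo gastrectomy is also conditioned on an event after open-label allocation.** This is true, so it needs an all-randomised analysis beside it. It does at least put the same question to both arms.

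**Conclusion.** The concern holds as a structural fault. The article ties its conclusion to a set whose entry condition only one arm can fail, in an unblinded trial, and names no analysis of all randomised patients. This is a stated rule, not a detail left to an analysis plan.

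Neither the size nor the direction of the bias can be settled from the documents. It is zero if starters and non-starters carry equal infection risk. Under the assumed 2–10% non-starters at 50–60% risk it is about 0.2 to 2.3 points in favour of the probiotic, with one-sided type I error of 0.027 to 0.060 against zero difference. It would be inferring too much to say that the primary result is invalid, or that it must favour the probiotic. The set should be corrected because the flaw lies in the main analysis and is cheap to remove, not because a large bias has been shown.

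**What to change.** Remove the receipt condition from the primary set. Analyse patients in the arm assigned, whether or not any capsule was taken, under one criterion identical in both arms. Two choices are defensible:

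- all randomised patients; or
- because the endpoint is postoperative, all randomised patients who undergo gastrectomy, supported by a sensitivity analysis in all randomised patients.

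Wherever all randomised patients are analysed, state how those not operated on are counted. Keep capsule adherence for the per-protocol set.

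Trial status says that recruitment is complete and the trial has ended, and the monitoring section has interim results released to all investigators. The change should therefore be dated and justified, and the result in the mITT set as the article defines it reported alongside. The number who never started should be given.

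The cost is a rewording and one further analysis, with N = 318 unchanged. It assumes that 30-day outcomes were collected for non-starters, which the article does not say. Retaining non-starters dilutes the effect. The dilution is slight if they are few, but at the assumed 10% the power against the threshold would be 67%.
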